## Abstract

**Background:**

Violence against women and girls (VAWG) is an urgent global health problem. Root causes for VAWG include the individual- and family-level factors of alcohol abuse, mental health problems, violence exposure, and related adverse experiences. Few studies in low- and middle-income countries (LMIC) have assessed the effectiveness of psychological interventions for reducing VAWG. This randomized controlled trial, part of the *What Works to Prevent Violence Against Women and Girls* consortium, examines the effectiveness of a common elements treatment approach (CETA) for reducing VAWG and comorbid alcohol abuse among families in Zambia.

**Methods/design:**

Study participants are families consisting of three persons: an adult woman, her male husband or partner, and one of her children aged 8–17 (if available). Eligibility criteria include experience of moderate-to-severe intimate partner violence by the woman and hazardous alcohol use by her male partner. Family units are randomized to receive CETA or treatment as usual. The primary outcome is VAWG as measured by the Severity of Violence Against Women Scale, assessed along with secondary outcomes at 24 months post-baseline. Interim assessments are also conducted at 4–5 months (following CETA completion) and 12 months post-baseline.

**Conclusions:**

This ongoing trial is one of the first in sub-Saharan Africa to evaluate the use of an evidence-based common elements approach for reducing VAWG by targeting a range of individual- and family-level factors, including alcohol abuse. Results of this trial will inform policy on what interventions work to prevent VAWG in LMIC with local perspectives on scale up and wider implementation.

## Background

Violence against women and girls (VAWG) is a recognized global health and human rights problem. In 2010, approximately one in three adult women were estimated to have experienced either physical or sexual intimate partner violence (IPV) in their lifetime (Devries *et al.*
2013). For a substantial proportion of these women, the physical violence experienced is severe, and poly-victimization is common (Garcia-Moreno *et al.*
2006). A recent systematic review of population-based surveys identified that approximately half of children in Asia, Africa, and North America experienced some form of violence in the past year, with violence in the home the predominant form for children between the ages of 2 and 14 (Hillis *et al.*
2016). Global prevalence estimates indicate that child sexual abuse victimization occurs in approximately one out of every eight children (Stoltenborgh *et al*. 2011). In a multi-national study, Zambia, the location of the present study, was found in a multi-national study to have the highest percentage of ever married women reporting IPV (48%) (Kishor & Johnson, 2004), and our own studies indicate that a substantial percentage of youth are exposed to a high number and wide range of violence experiences (Murray *et al.*
2006, 2015).

Violence has many repercussions. IPV in women is associated with severe injury, gynecological problems, chronic pain, increased risk of sexually transmitted infections (including HIV), poorer overall self-rated health, alcohol use, post-traumatic stress, depression, anxiety, and suicidal ideation, with more severe symptoms linked to poly-victimization (Campbell, 2002; Ellsberg *et al.*
2008; Trevillion *et al.*
2012; Dillon *et al.*
2013; Devries *et al.*
2014; Lagdon *et al.*
2014; Li *et al.*
2014). Experiencing abuse and witnessing violence as a child are associated with a wide range of negative outcomes, including injury, developmental deficits, risk-taking behaviors, poor physical health, mental health problems, and death (Campbell & Lewandowski, 1997; Felitti *et al.*
1998; Springer *et al.*
2007; Irish *et al.*
2010). Further, research shows that witnessing or experiencing violence within the home predicts victimization and perpetration of violence in later life (Abramsky *et al.*
2011; Fulu *et al.*
2013; Fonseka *et al.*
2015).

Partner alcohol abuse is a strong predictor of experiencing IPV (Abrahams *et al.*
2004; Jewkes *et al.*
2006; Capaldi *et al.*
2012). Women whose husbands frequently return home drunk have an increased risk of experiencing abuse (Abramsky *et al.*
2011; Fulu *et al.*
2013). The role of alcohol use in IPV perpetration and experience is a particular concern in low- and middle-income countries (LMIC), specifically in sub-Saharan Africa, where rates of problematic alcohol use are increasing (Shield *et al.*
2013). Mental health problems, particularly depression and post-traumatic stress disorder, have also been associated with experiencing (Iverson *et al.*
2011; Kuijpers *et al.*
2012) and perpetrating (Fulu *et al.*
2013; Oram *et al.*
2014) violence.

Economic and social ‘structural’ interventions have demonstrated effectiveness for addressing some risk factors (e.g. inequitable gender norms) of violence, but findings for actual reductions in its occurrence are mixed (Bourey *et al.*
2015). Although these structural interventions are essential to broad primary prevention of IPV, the complex inter-relationship between violence, alcohol, and mental health suggests a need for integrated approaches that include treatments targeting high-risk groups (Guedes *et al.*
2016). Two trials conducted in the USA suggest cognitive–behavioral therapy (CBT) interventions and alcohol treatment combined with violence prevention programs show promise for impacting some types of IPV (Tirado-Muñoz *et al.*
2014; Wilson *et al.*
2014). Given the high rate of IPV in LMIC and the dearth of evidence-based interventions in these settings, more studies are needed to evaluate approaches that address high-risk families affected by IPV, alcohol use, and/or mental health problems.

This paper describes: (1) the process of adapting an evidence-based, modular transdiagnostic treatment approach (common elements treatment approach; CETA) (Murray *et al.*
2014) to address violence and alcohol abuse, and (2) the protocol for testing CETA in an ongoing randomized controlled trial. The trial is part of a larger consortium of studies, the *What Works to Prevent Violence Against Women and Girls Programme* (http://www.whatworks.co.za/), investigating the underlying causes of VAWG and strategies for prevention in LMIC. The primary aims of the trial are to evaluate the effectiveness of the adapted CETA intervention on (a) reducing and preventing women's experience of IPV and (b) reducing male partner's hazardous alcohol use.

## Methods/design

### Overview of study design

The Violence and Alcohol Treatment (VATU) study (*vatu* means ‘ours’ in Nyanja, a commonly spoken language in Zambia) is a parallel group randomized clinical trial comparing the effectiveness of CETA to treatment as usual (TAU) among family ‘units’ consisting of three individuals: an adult woman, her male husband or partner, and one of her children (male or female, ages 8–17). The study settings are three high-density, low-resource ‘compounds’ (i.e. neighborhoods) in Lusaka. Eligible families are randomized as a unit to CETA or to TAU. All participants are assessed at four time points: (1) baseline; (2) 4–5 months (following CETA completion); (3) 12 months; and (4) 24 months post-baseline. The study flow is illustrated in Fig. 1.

**Fig. 1. fig01:**
[figure not shown]
Flow of study procedures for VATU trial.

### Ethical approval and trials registration

The study has been approved by the Johns Hopkins Bloomberg School of Public Health Institutional Review Board and the University of Zambia Biomedical Research Ethics Committee. The trial is registered at ClinicalTrials.gov (NCT02790827; date of registration 05/24/2016). The study methods described below cover the recommended items to address in a clinical trial protocol according to SPIRIT (Chan *et al.*
2013).

### Recruitment

Initial recruitment, screening, baseline assessment, and randomization for the study were conducted between May and July 2016. Following principles of community-based participatory research, our research staff met with community leaders in each compound to discuss the purpose and procedures of the trial prior to its initiation and organized larger meetings open to the community where questions and concerns about the study were addressed. We have found in previous studies in Zambia that this type of community involvement is essential to success (Murray *et al.*
2006; Kane *et al.*
2016*b*). This approach also enabled collaboration with local leaders in identifying community members who they felt were suitable candidates for being hired and trained as CETA counselors. Recruitment of study participants was subsequently conducted by these study counselors. This provider-based recruitment strategy was employed because it is the current method for outreach used by our partnering organization in Zambia for similar behavioral interventions and it has been found to be culturally acceptable and feasible for potentially sensitive topics, such as alcohol use.

Counselors received a 1-day training in recruitment procedures before going door-to-door in their communities with a script to assist in explaining the purpose of the study to families. Counselors worked in male/female pairs when visiting families’ homes, so that women could speak alone to a counselor of the same sex. To ensure that participation in the study would not exacerbate or lead to IPV, counselors specifically asked the women about possible risks. If the woman expressed concern for her safety, the counselor offered her information on, or assistance in, accessing services. Women with a child between the ages of 8–17 were asked if they would like to provide permission for the child to participate. Women with more than one child were encouraged to select the child whom they perceived as being most affected by the violence in the home. Families without a child in this age range or those that did not want a child to participate were still able to join the study as a couple.

### Eligibility screening

Families who expressed interest in the study were invited to participate in an eligibility screening at a later date, typically within 1 week, at a site in their community (i.e. school, church, or community center). Study assessors met with families privately and provided a brief overview of the purpose and procedures of the study to all family members (i.e. the woman, man, and child). Informed consent was then obtained with each family member separately in a private space. Consent was obtained for all study activities (screening, assessments, and intervention).

Following informed consent, the woman and her male partner separately completed an eligibility screener. For women, this consisted of the Severity of Violence Against Women Scale (SVAWS; Marshall, 1992), for assessing recent IPV; and the Alcohol Use Disorders Identification Test (AUDIT; Saunders *et al.*
1993), for measuring her report of her partner's hazardous drinking. Men only completed a self-reported AUDIT. To be eligible, (a) the woman had to report recent (past 12 months) experience of at least a moderate level of violence (SVAWS physical violence subscale score of ⩾38) and (b) she or her partner had to report that he has engaged in hazardous alcohol use (AUDIT score of ⩾8). Additional eligibility criteria are detailed in Box 1.
Box 1.Inclusion and exclusion criteria for the VATU trial.Inclusion criteria
The family must live in one of the three study compounds in Lusaka (i.e. cannot only be staying temporarily).All family members must speak at least one of the three study languages: English, Bemba, or Nyanja.The family must consist of an adult (aged 18 years or older) female and adult male in a relationship (i.e. married or dating). In addition, the woman has the choice (if applicable) to identify one of her children between the ages of 8 and 17 for inclusion in the study.Both the adult female and her male partner must provide consent. For one of her children to also participate, the woman's permission and the child's assent are required.The adult female must score 38 or more on the Severity of Violence Against Women Scale (SVAWS; physical violence subscale) indicating experience of at least a moderate amount of intimate partner violence.The adult male must have a score of 8 or higher on the Alcohol Use Disorders Identification Test (AUDIT) as reported by himself or his partner, indicating that he drinks alcohol at hazardous levels.Exclusion criteria
No family member can currently be on an unstable (i.e. altered in last 2 months) psychiatric drug regimen.No family member has had a suicide attempt or suicidal ideation accompanied by intent, a plan, or self-harm in the past month.No family member has been diagnosed with a current psychotic disorder (identified by the University of Zambia Teaching Hospital Psychiatric Unit).No family member has a serious developmental disorder (e.g. mental retardation, autism) that would preclude participation in a cognitive-behavioral oriented skills intervention or completing the assessment battery.

The screener was administered using a laptop-based Audio Computer Assisted Self-Interviewing (ACASI) system. ACASI was chosen for use because previous studies have found that it elicits more valid responses to questions on sensitive behaviors than face-to-face interviewing and because it is feasible and acceptable among this study population (Langhaug *et al.*
2010; Kane *et al.*
2016*a*, *b*). ACASI scored the screener immediately, and if the family was determined to be eligible, the assessor administered the full assessment battery (approximately 2 additional hours total; see Assessments section below) separately to all participating family members. If the family was ineligible, the assessor discussed services in the community that may be appropriate. Following administration of the full ACASI, any participant who reported suicidal ideation, homicidal ideation, or who was currently experiencing violence, was flagged as ‘high risk’. ACASI automatically alerted the assessor about the high-risk status, and the assessor immediately activated a standardized safety plan (included in full as online Supplementary material and summarized in Box 2).
Box 2.Summary of VATU study participant safety protocol.
Assessing and responding to suicide risk
Evaluate suicide risk
Are you thinking about killing yourself or ending your life?Have you ever tried to kill yourself or end your life?Do you have a plan to kill yourself or end your life?Do you have access to that plan; in other words, do you have the means to execute your plan?Response
If the client answers yes to any of these questions call your supervisor immediately while the client is still working with you. Decide and agree on a plan before the client leaves.Safety planning may include creating a safety contract with the client, identifying warning signs and coping skills, using safety watch and imminent risk referrals to the closest facility where the client can be monitored more closely.Assessing and responding to homicide risk
Assessing homicide risk
Have you ever tried to end someone's life/hurt someone before?Are you thinking about ending someone's life/hurting someone?Do you have a plan to end someone's life/hurt that person?Do you have access to that person; in other words, do you have the means to execute your plan?Response
If a client answers ‘YES’ to any of these questions, immediately inform the clinical supervisors. Staff will arrange for the person to be accompanied to a safe place, and will call her/his supervisor ahead to advise the supervisor of the situation.Safety planning may include safety contracts, safety watch, and where needed reporting to local authorities and referral for observation.Assessing and responding to interpersonal violence risk
Evaluate interpersonal violence risk
Is the person being violent in the home (e.g. hitting, kicking, etc.) living with you?In what ways has this person hurt you?In what ways do you think this person could hurt you?Response
The staff will talk to her/his supervisor while the participant is still working with them. The staff and the participant will decide or agree on a plan BEFORE the participant leaves the session.Safety planning varies based on local laws but may include reporting to victim support unit of the police, referral to a shelter or gender based violence one-stop center or safety prevention plans in the home.Assessing and responding to child abuse risk
Evaluate child abuse risk
Do you know the person who is abusing you?Does the abuser stay in the same house with you?Have you reported to anybody?If you have reported, what has been done?Response
If the client answers ‘YES’ to the first three questions, immediately call designated contacts at Social Welfare and the Child Protection Unit of the police. The staff shall ensure to call their supervisor at the end of the session before the client leaves.If the client says no to the first questions ask for more information. For example: When was the last time the abuse happened? Where is the person who was abusing you currently staying? Does anyone in the home know about the abuse?Safety planning may include working with families and authorities to find a safe placement for the child while investigations are taking place.

### Randomization and blinding

All participants were assigned a unique ID number following informed consent procedures. ID numbers of eligible participants were forwarded from the assessors to the Zambia-based study director at the end of each day, who then sent them to a designated US-based research staff member who was not involved in clinical activities. The US-based staff member maintained a computer-generated (via Microsoft Excel) 1:1 randomization sequence stratified by study compound and in blocks of 20 (i.e. each 20 assignments included 10 CETA and 10 TAU). Each of the three lists contained a sequence of treatment assignments in random order. These lists were not available or viewable to any staff in Zambia. The US-based research staff member would assign a family to the next available slot on the randomization sequence. Eligible families were contacted within a day of randomization to inform them of their status. Study assessors and data analysts were masked to randomization status at the baseline assessment and will remain blinded throughout the duration of the study.

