### Data analysis

Sample size calculations were informed by a study conducted in South Africa that used the SVAWS physical violence subscale to measure violence among women who had been abused by a partner with an alcohol use problem (Peltzer & Pengpid, 2013). We calculated the sample size needed to obtain a 20% reduction in SVAWS physical violence subscale score among intervention participants at a 24-month follow-up, assuming no change among control participants, using a two-sample independent means *t* test. For 80% power at an *α* level of 0.05, we calculated that we would need to enroll a minimum of 50 families in each study arm to detect this difference in change in means, which we inflated to 84 per arm to account for loss to follow-up and the possibility of small clustering effects at the provider level.

All primary analyses will be based on an intent-to-treat approach with all participants who were randomized included in the final analysis. Loss to follow-up and missing data will be addressed by using multiple imputation (Azur *et al.*
2011). We will estimate linear (continuous outcomes) and generalized linear (binary outcomes) mixed-effects models that will incorporate a random intercept term to account for within-subject correlation on repeated measures. The outcome scores at the three follow-up times will be modeled separately using treatment arm, baseline symptom score (if there is a meaningful difference between the study arms at baseline), time, and an interaction between each treatment arm and time as fixed covariates in each model.

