### Modification to study protocol after initiation of the trial

We modified the delivery of CETA from group to individual. After the first few weeks of intervention delivery, multiple participants were missing group sessions due to logistical challenges (e.g. work, funerals), which necessitated CETA providers to conduct separate individual sessions for participants that were absent. It became challenging for providers to keep up with the many in-between group sessions they had to conduct, and then also had to repeat material in groups if an individual missed and was not available in-between group sessions. Participants also indicated frustration in that they did want to participate but there was no flexibility for tardiness (in Zambia, this may be defined as an hour or more late) or work/family scheduling within groups. The challenges were substantial enough that we would not recommend group CETA in Lusaka, Zambia (urban area), even if it was found to be clinically effective. We therefore modified CETA to be individually delivered. Participants initiating CETA before this change could switch to receiving individually delivered CETA or continue to attend group sessions based on their preference and the counselor's assessment of feasibility.

We increased our sample size because of this modification to the delivery of CETA. We plan to conduct a subgroup analysis of only those study participants who received individual (and not group) CETA to test whether this individual delivery mode is effective compared with the TAU control group. Of the 83 families originally randomized to CETA, 33 men and 40 women did not receive a group session (only individual session or sessions). Our original sample size calculation for the CETA arm was *n* = 50. To have at least *n* = 50 CETA participants who received individually delivered therapy, and taking into account potential for up to 30% loss to follow-up, we recruited and randomized an additional 80 families (again randomizing using 1:1 allocation). The final sample size for the study is thus *n* = 248. All the families recruited in this second cohort that were randomized to the CETA arm are receiving individually delivered CETA.

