### Trial status

Recruitment, screening, and randomization of all study participants were completed in December 2016. The first wave of recruitment occurred between May and July 2016 and the second wave (following the sample size increase) occurred between November and December 2016. Participant baseline characteristics are summarized in Table 3. All participants are expected to complete the CETA intervention and first post-assessment by April 2017. The 12-month post-assessment will occur between May and July 2017 for the first cohort of families recruited and between November and December 2017 for the second cohort. The 24-month post-assessment will occur between May and July 2018 and between November and December 2018 for the first and second cohorts, respectively.

**Table 3. tab03:** Baseline participant characteristics

	Adult female (*n* = 248)	Adult male (*n* = 248)	Child (*n* = 130)
Age			
18–25	65 (26.2)	27 (10.9)	
26–35	99 (39.9)	94 (37.9)	8–9 28 (21.5)
36–45	49 (20)	74 (29.8)	10–11 33 (25.4)
46–55	25 (10.1)	37 (14.9)	12–13 30 (23.1)
56–65	7 (2.8)	11 (4.4)	14–15 20 (15.4)
66+	2 (0.8)	5 (2.0)	16–17 19 (14.6)
Female	–	–	70 (53.9)
HIV positive	101 (40.7)	66 (26.6)	12 (9.2)
SVAWS physical violence subscale, mean (s.d.)	60.7 (16.8)	–	–
Child abuse (physical)^a^	–	–	54 (41.5)
Child abuse (verbal/emotional)^b^	–	–	49 (37.7)
AUDIT (self-report), mean (s.d.)	10.7 (11.0)	15.8 (10.4)	–
Lifetime substance use^c^	116 (47.0)	159 (64.4)	–
Harvard Trauma Questionnaire (HTQ), mean (s.d.)	1.5 (0.7)	1.3 (0.7)	–
Child PTSD Symptom Scale (CPSS), mean (s.d.)	–	–	0.7 (0.7)
Center for Epidemiological Studies-Depression (CES-D), mean (s.d.)	2.2 (0.7)	2.0 (0.6)	–

Values are *n (%)* unless otherwise specified and based on all available data at baseline

a Response of once, sometimes, or often, to item ‘how often have you been beaten at home in the past 12 months’

b Response of once, sometimes, or often to item ‘how often have you been verbally or emotionally abused at home in the past 12 months’

c Any lifetime substance use reported not including alcohol or tobacco on the Alcohol, Smoking, and Substance Involvement Screening Test

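### Randomisation was stratified by compound and recruitment ran in two waves, but the stated model includes neither factor; if they predict SVAWS, the reported standard error is too large and the primary test is conservative

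*Protocol article*

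**What the plan says.** **Allocation.** Randomization and blinding gives a "1:1 randomization sequence stratified by study compound and in blocks of 20". There was one list per compound: "Each of the three lists contained a sequence of treatment assignments in random order".

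**Second wave.** After CETA delivery moved from group to individual sessions, the section on modification of the protocol reports: "we recruited and randomized an additional 80 families (again randomizing using 1:1 allocation". Trial status places the first wave in May to July 2016 and says that "the second wave (following the sample size increase) occurred between November and December 2016". Delivery differs between the waves. In the first it was mixed; for the second, "All the families recruited in this second cohort that were randomized to the CETA arm are receiving individually delivered CETA". The total is given as "The final sample size for the study is thus *n* = 248".

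**Model.** Data analysis specifies mixed-effects models with a random intercept for repeated measures. The fixed terms are treatment arm, baseline score (only if the arms differ meaningfully at baseline), "time, and an interaction between each treatment arm and time as fixed covariates in each model". The section that adds the second wave plans a subgroup analysis of individually delivered CETA, but does not revise this model.

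**The concern.** When arms are balanced on a factor that predicts the outcome, differences between levels of that factor no longer contribute to chance differences between the arms. A model that omits the factor still counts those differences as residual noise. Its standard error is then larger than the true sampling variation of the estimate, confidence intervals are too wide, and the test rejects less often than it should.

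The article does not leave the covariates open. It lists them, and the list omits the one stated stratification factor. Recruitment wave is a second known feature of the design: the waves were randomised months apart, and the CETA arm was delivered differently in each. At stake is some avoidable loss of power on the primary outcome.

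**Working it through.** **Inputs from the article.** Three compound lists, blocks of 20, 1:1 allocation; 80 families in the second wave; 248 in total; alpha 0.05 (two-sided assumed).

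**Input not in the article.** The share *s* of outcome variance that compound and wave explain beyond the other model terms. I assume 0%, 2%, 5% and 10%, and add 20% as an outer value in the simulation.

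**The plan's own figures.** The total reproduces: 2 × 84 + 80 = 248. The 50 per arm cannot be reproduced, because the planning mean and SD come from a cited study and are not given. With a two-sample *t* test at 80% power, 50 per arm implies a standardised difference of about 0.57. Nothing in this point shows that number to be wrong.

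**Closed form** (outcome SD scaled to 1, arms balanced within levels):
- Standard error reported without the factors: √(4/248) = 0.127.
- Actual sampling SD: √(4(1 − *s*)/248).
- Overstatement: 1/√(1 − *s*) − 1.
- Actual type I error: 2·P(Z > 1.96/√(1 − *s*)).

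| *s* | SE overstated by | 1.96/√(1 − *s*) | Type I error |
|---|---|---|---|
| 0% | 0% | 1.960 | 5.0% |
| 2% | 1.0% | 1.980 | 4.8% |
| 5% | 2.6% | 2.011 | 4.4% |
| 10% | 5.4% | 2.066 | 3.9% |

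**Simulation.** 168 + 80 families, three compounds of near-equal size, separate permuted blocks of 20 in each compound and wave, *s* split equally between compound and wave, and one continuous outcome analysed by least squares without and with the factors. There were 25,000 null runs per setting. Power used 10,000 runs per setting (4,000 at *s* = 0) at *d* = 0.36, about the difference with 80% power at this size: (1.96 + 0.84) × 0.127 = 0.356.

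| *s* | Reported SE, without / with | Sampling SD of estimate, without / with | Type I error, without / with | Power, without / with |
|---|---|---|---|---|
| 0% | 0.127 / 0.127 | 0.127 / 0.127 | 5.1% / 5.2% | 81.7% / 81.9% |
| 5% | 0.127 / 0.124 | 0.124 / 0.124 | 4.4% / 4.9% | 81.0% / 82.2% |
| 10% | 0.127 / 0.1205 | 0.121 / 0.120 | 3.9% / 4.7% | 81.7% / 84.5% |
| 20% | 0.127 / 0.114 | 0.115 / 0.113 | 3.1% / 4.9% | 83.2% / 88.7% |

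The simulation agrees with the closed form at 5% and 10%. The article does not say whether the compound lists were restarted or continued for the second wave. A smaller run with continued lists gave a similar picture: at *s* = 10%, type I error was 4.1% without the factors and 4.9% with them.

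**What an arm-by-wave interaction could show.** Its standard error, with full retention, is √(4/168 + 4/80) = 0.27 SD. A difference in effect of about 2.80 × 0.272 = 0.76 SD between the waves would be needed for 80% power.

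**The case against.** The strongest reply is that the harm is conditional and small. The article gives no figure for how much SVAWS variance compound or wave explains. At zero, nothing changes. Even when the factors matter, the estimate itself is hardly less precise, because stratified allocation has already supplied the balance. This stands, and it sets the size of the point: what is wrong is mainly the reported standard error. A reader might translate *s* × 248 into 5, 12 or 25 families thrown away. That describes the width of the reported interval, not information actually lost, and 25 is reached only at the 10% share.

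Three other stronger readings are not supported:

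- **Wave as a stratification factor.** The article names compound only. Wave is a feature of how the trial was run, and the case for including it rests on that.
- **Pooling conceals the change of delivery.** The article discloses the change, plans a comparison of individual-only CETA with usual care, and enlarged the trial to support it. Wave is also a poor stand-in for delivery mode: "Of the 83 families originally randomized to CETA, 33 men and 40 women did not receive a group session". The shift in calendar time and in the past-year recall window affects both arms alike, since allocation is 1:1 in each wave and follow-up is timed from baseline.
- **The imputation model and the DSMB's 12-month analysis are also deficient.** The article does not give the terms of either model, so their absence there is detail left to a fuller document.

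The conditional baseline score and the random intercept may also absorb some of the variance between compounds. For that reason *s* is defined as the share beyond the other terms. The simulation used a single outcome without baseline, so it illustrates the size for a given share and does not estimate that share.

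It can also be said that a condensed article leaves covariates to the analysis plan. That would answer silence. Here the covariates are listed, and the list omits the stratification factor.

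**Conclusion.** The point holds in a limited form. The stated model does not reflect the stratified randomisation or the two recruitment waves. If those factors predict SVAWS, the primary analysis is conservative: for shares of 0% to 10%, the standard error is overstated by 0% to 5.4%, the type I error is 5.0% down to 3.9%, and about 0 to 3 points of power are lost. At the outer value of 20%, the loss is about 5 points.

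A reader might infer that the primary result would be biased or falsely significant. It would not: allocation is 1:1, and the error runs towards too few rejections. The omission is certain from the text. Its size rests on the assumed variance shares, and the arithmetic applies to continuous outcomes, including the primary one. The sample size needs no change on this account.

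**What to change.** In Data analysis, add compound (three levels) as a fixed effect in the primary and secondary outcome models, stated as the stratification factor and included whatever its observed balance or significance. Add recruitment wave (two levels) as a design covariate.

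The cost is a sentence of wording and 2 + 1 = 3 degrees of freedom out of 248 families. Both variables are known for every family. If neither factor is prognostic, the simulation shows essentially no penalty.

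An arm-by-wave interaction may be reported descriptively. It has low power, so a null result would not show that pooling is safe, and it does not replace the individual-delivery subgroup analysis already planned.
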